### Blinding

The investigators, data collectors, study observers, data entry operators and data analysis statistician will be blinded to the allocation. The patients will not be blinded to the pharmacists; however, they will be blinded to the intervention. The data collector will not know if the patient belongs to the IG or CG. The pharmacist will be blinded to the outcome assessment so that there will be less likelihood of intervention bias. The blinding scheme is shown in Table 1.

**Table 1 Tab1:** Blinding scheme

Stake holders	Allocation scheme	Intervention allocation room	Pharmacist intervention	Data form color code	Outcome assessment	Data analysis
Study observers	A	NA	A	A	A	A
Study officer	NA	NA	NA	NA	NA	NA
Patients	NA	NA	NA	NA	NA	NA
Pharmacists	NA	NA	A	NA	NA	NA
Rheumatologists	NA	NA	A	NA	NA	NA
Data collectors	NA	NA	NA	NA	NA	NA
Data analysis technicians	NA	NA	NA	NA	NA	A

*A* Aware, *NA* Not aware

### Eligibility criteria for selection and training of pharmacists

An eligibility criterion has been outlined for pharmacists who would participate in the study. The minimum requirements for a pharmacist to be eligible to participate in the study and to be able to deliver the intervention were layed out. The applicant would be a graduate with Doctor of Pharmacy, i.e., Pharm.D degree obtained from an institute recognized by the Pharmacy Council of Pakistan [18]. The applicant should be registered as ‘Pharmacist’ in category, ‘A’, by the pharmacy regulatory body [19]. The registration certificate should be valid at the time of applying for participating in this study.There are two types for bachelor’s degrees awarded to pharmacists in Pakistan. The Bachelor of Pharmacy, i.e., B.Pharm and Doctor of Pharmacy, i.e., Pharm.D. The B.Pharm is a four-year degree while Pharm.D is relatively new degree that is completed over a course of five years with a residency component if the candidate wants to pursue a career in health sector. The Pharm.D degree has more clinically oriented courses and students learning is enhanced through clinical rounds [20]. Therefore, Pharm.D graduates would be included. The registration by regulatory body is important as it would be required in clinical practice. All applicants who lack in any of the abovementioned criteria would be excluded from study.The pharmacists involved in the study will be trained. A total of eight lectures of 1-h duration is planned over a span of 2 weeks to be given to participating pharmacists. These lectures will focus on selected topics on RA disease that are deemed important and helpful while educating patients. These will include disease epidemiology in Pakistan, symptoms and risk factors, brief information about diagnosis and treatment, the importance of physical therapy and rehabilitation, the importance of adherence to treatment and self-care techniques. Training will also include a lecture on the pharmacist’s role in self-care and home-based disease management and a lecture to reinforce patient counselling skills for pharmacists. The training will also encompass detailed briefing on the study protocol and administering the intervention. The training module and disease education literature will be provided to all pharmacists for the purpose of self-study at home. An assessment test based on the lectures will be conducted at the end. The training presentation is available as Additional files 4 and 5. Disease education literature for patients is available as Additional file 6.

### Intervention

The intervention consists of a pharmacist providing pharmaceutical care that will be in the form of an educational intervention. It will be delivered by the pharmacist as a single, face-to-face, structured session of 20–25 min duration. Moreover, specially designed RA disease education literature will be provided in both the Urdu and English languages for patients to use at home. An intervention delivery plan consisting of a checklist has been developed to assure uniformity of the intervention delivered to patients. The plan is available as Additional file 7.

A specially designated counselling area in the rheumatology clinic serves as a venue for the intervention. The schedule of enrollment, intervention and assessment is provided in Fig. 2. The implementation will be observed by utilizing mixed models with random intercepts for pharmacists. The variance fraction explained will be observed by calculating the intraclass correlation coefficient using unconditional and conditional models [21].

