## Methods/design

### Design and setting

This study is a randomized, single-blind, parallel trial. The patients who participate in this study after providing signed consent would be randomly assigned to either the control group (CG), i.e., usual care, or intervention group (IG), i.e., pharmaceutical care. The allocation ratio will be 1:1. The participants in the IG would receive an educational intervention delivered by the pharmacist and provided with disease education literature. The participants in the CG would receive usual care without pharmacist intervention. The usual care in Pakistan’s healthcare system encompasses an appointment with a physician, which does not include pharmaceutical care. Usually, a pharmacist is limited to dispensing medicines to patients.

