### Recruitment strategy

The patients will be recruited from the rheumatology departments at three tertiary care hospitals located in city of Karachi, Pakistan. Patients will be recruited through an advertisement displayed at the reception counters. The recruitment advertisement is still ongoing. A study officer would administer the consent form, which is available in both the English and Urdu languages, and enroll consenting patients in the study. The list of study sites is available as Additional file 3.

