### Sample size

Few randomized controlled trials have evaluated the effect of pharmacists’ educational interventions on adherence and disease knowledge among patients with RA. We reviewed several studies that could serve as a reference for calculation of sample size based on treatment effect. A study conducted by Clifford and colleagues assessed the effect of pharmacist educational advice on improving adherence [7]. Another study by Stockl and colleagues was nonrandomized and was limited to evaluating the effects of a telephone intervention by either a pharmacist or a nurse, on patients’ adherence to injectable RA medicines [8]. Azzopardi and colleagues used a different outcome measure to ours and included patients with RA prescribed methotrexate only [28]. Similarly, in another RCT, Petkova measured a different outcome [3].

We considered a study by Clifford and colleagues as a standard and calculated our sample size based on the primary outcome, i.e., adherence [7, 29]. It was taken as a reduction in self-reported nonadherence from 16% to 9% considering a (two-side) alpha value of 0.05 and statistical power of 80%, i.e., beta = 0.2. Considering a drop-out rate of 20%, we would require a total of 619 patients to successfully demonstrate a positive and statistically significant effect.

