### Statistical analysis

The statistical analysis will be conducted by a statistician who will be blinded to patient-group allocation. The analysis will be carried out using SPSS version 22 (IBM SPSS, Armonk, NY, USA). The analysis will consist of a per-protocol set that includes participants who have completed the study as per the defined protocol. The significance level will be set at 5% and a two-tailed test will be used. Continuous data will be descriptively analysed using the Mann-Whitney U test, while the chi-square test will be used to analyze categorical variables by comparing them in the two groups at the same time point. Confirmatory analysis will be carried out using the Wilcoxon signed-rank test to analyze differences in the mean values for disease knowledge, adherence to treatment and medications and the cost of treatment after 3 months, i.e., baseline within-subject analysis. Multinomial logistic regression will be used to interpret the odds ratios for the secondary outcome, i.e., patient satisfaction with pharmacist counselling. There will be no interim data analysis.

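### The plan models between-pharmacist variation only to observe implementation; its effect tests and sample size ignore it, so p-values are too small if outcomes depend on the pharmacist

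*Protocol article*

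**What the plan says.** All places are in the protocol article.

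- **Intervention.** The session is face to face, structured and 20–25 minutes long, and follows a checklist meant to keep delivery uniform. Then: "The implementation will be observed by utilizing mixed models with random intercepts for pharmacists". And: "The variance fraction explained will be observed by calculating the intraclass correlation coefficient using unconditional and conditional models". No trial outcome is named as the response, no arm term is mentioned and no ICC value is anticipated.
- **Eligibility criteria for selection and training of pharmacists.** Pharmacists are referred to in the plural, with common lectures and a closing test. Their number is not given.
- **Design and setting; Randomization and allocation concealment.** Patients are randomized individually, 1:1. Intervention patients meet a pharmacist; control patients do not.
- **Recruitment strategy.** Patients are "recruited from the rheumatology departments at three tertiary care hospitals".
- **Statistical analysis.** Continuous data are compared between groups descriptively by Mann-Whitney U, and categorical data by chi-square. "Confirmatory analysis will be carried out using the Wilcoxon signed-rank test", within subject. None of these tests carries a pharmacist or hospital term.
- **Sample size.** The inputs are a "reduction in self-reported nonadherence from 16% to 9" per cent, two-sided alpha 0.05 and 80% power. "Considering a drop-out rate of 20%, we would require a total of 619 patients". There is no design effect.

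**The concern.** Intervention patients counselled by the same pharmacist share whatever that pharmacist does better or worse than colleagues. Control patients have no such grouping. Clustering can therefore arise in one arm only, which is a partially nested design. A face-to-face counselling session is the kind of treatment whose effect can depend on who delivers it, and the article provides a way to measure that dependence.

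The measurement is not carried into inference. Every test named for the effect treats patients as independent, and so does the sample size. If patients of one pharmacist are correlated in outcome, the variance of the intervention-arm mean is larger than these tests assume. A result could then be declared significant at 5% when the real error rate is higher, and the power would be lower than stated.

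This goes beyond detail left to a fuller document. The article itself states both the pharmacist model and the effect tests, and the two are not connected.

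**Working it through.** **1. The plan's own figure, with independent patients.** Inputs from Sample size: 16% against 9%, two-sided alpha 0.05, power 80%, dropout 20%, allocation 1:1. The usual two-proportion formula is

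n per arm = [1.96·√(2·0.125·0.875) + 0.842·√(0.16·0.84 + 0.09·0.91)]² / 0.07² = 349.2, rounded up to 350.

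That is 700 in total, and 700/0.8 = 875 with dropout. The stated 619 is not reproduced. Other two-sided variants without continuity correction give 826 to 878 after dropout. With 619 × 0.8 ≈ 495 completers, power is 65.4% before any clustering. That shortfall is a separate matter. What counts here is that no version of the calculation contains an allowance for pharmacists.

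**2. Inputs for the clustering check.** Intervention completers: 619 × 0.8 / 2 ≈ 247, with the same number of controls (from the plan). Number of pharmacists k and ICC: not given, so assumed as k = 12, 6 or 3 and ICC = 0.01, 0.02 or 0.05. The ICC is taken as the pharmacist-specific part of outcome variation.

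**3. Formulas**, for a between-arm test that ignores pharmacist:

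- design effect in the intervention arm: DE = 1 + (247/k − 1)·ICC
- true over assumed standard error of the difference: R = √((DE + 1)/2), since only one arm is clustered
- type I error = 2·(1 − Φ(1.96/R))

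**4. Example, k = 6 and ICC = 0.02.** DE = 1 + (41.17 − 1)·0.02 = 1.80. R = √(2.80/2) = 1.18. Type I error = 2·(1 − Φ(1.655)) = 9.8%. The 247 patients carry the information of 247/1.80 ≈ 137.

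**5. Results.**

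| Pharmacists | ICC | DE | R | Type I error |
|---|---|---|---|---|
| 12 | 0.01 | 1.20 | 1.05 | 6% |
| 12 | 0.02 | 1.39 | 1.09 | 7% |
| 12 | 0.05 | 1.98 | 1.22 | 11% |
| 6 | 0.01 | 1.40 | 1.10 | 7% |
| 6 | 0.02 | 1.80 | 1.18 | 10% |
| 6 | 0.05 | 3.01 | 1.42 | 17% |

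With ICC = 0 there is no inflation. The same arithmetic for k = 3 gives 10%, 15% and 26%. It is not used here: with one pharmacist per hospital, the pharmacist cannot be separated from the site, and site variation shared with controls does not inflate a between-arm comparison.

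**6. The test called confirmatory.** The table does not apply to the signed-rank test, which is within subject. If it is run within the intervention arm, no unclustered arm dilutes the effect, so R = √DE. With k = 6 and the ICC of change scores taken as 0.02, R = 1.34 and the approximate error is 14%.

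**7. What allowing for pharmacist would cost.** The Satterthwaite degrees of freedom are (1 + DE)² / (DE²/(k − 1) + 1/246), and interval width relative to the naive analysis is R·t/1.96.

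| Pharmacists | ICC | Degrees of freedom | t | Relative width |
|---|---|---|---|---|
| 12 | 0.01 | 36 | 2.03 | 1.08 |
| 6 | 0.02 | 12 | 2.18 | 1.32 |
| 3 | 0.05 | 2.9 | 3.27 | 2.9 |

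**The case against.** **The plan does not predict pharmacist differences.** A reader might infer that the authors expect outcomes to vary by pharmacist. The text does not support that. The model is tied to implementation, no outcome is named, and the checklist and common training aim at uniform delivery. Planning to estimate an ICC does not imply that it is above zero. This stands: the article provides for variation; it does not forecast it.

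**Type I error need not exceed 5%.** A reader might also infer that the planned tests are necessarily anti-conservative. Patients are randomized individually. If counselling by these pharmacists does nothing, the pharmacist creates no correlation and a between-arm test keeps its level. Inflation needs pharmacist-specific effects that average to zero over a wider population of pharmacists, together with a wish to generalise to that population. The article does not define its target that formally. This stands as a condition, although the Discussion does present the results as a foundation for future care in Pakistan and elsewhere.

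**The size is all assumption, for a test the plan calls descriptive.** This also stands. The figures illustrate a between-arm test and are not an estimate for this trial. Likewise, leaving hospital out of an individually randomized comparison is not in itself a source of type I error.

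**A condensed article may leave the link to a fuller document.** This has less force. The article commits to specific effect tests, including which one is confirmatory, and none can take a pharmacist term.

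**Conclusion.** The point holds in conditional form. The article sets up a pharmacist random effect and an ICC, then uses neither in the tests of effect nor in the sample size, although only the intervention arm is grouped by pharmacist. The planned p-values are too small if two things are true: the pharmacist-specific outcome ICC is above zero, and conclusions are to extend beyond the participating pharmacists.

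The size cannot be fixed from the document. Under the assumptions shown, it runs from negligible (6% instead of 5%) to material (17%). The repair is worth making because it costs little in work and also replaces a within-subject confirmatory test with a comparison between arms.

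**What to change.** Make the confirmatory analysis a between-arm model: week-12 score on arm, baseline score and hospital (fixed effects), with a random pharmacist intercept in the intervention arm only and small-sample degrees of freedom such as Satterthwaite. Report the ICC and the number of pharmacists. The method is one that the article already names, but the arm and baseline terms are new. The stated pharmacist model concerns implementation and does not include them.

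If there are too few pharmacists to estimate the variance, keep the between-arm model adjusted for baseline and hospital as primary. Show the pharmacist-clustered result as a sensitivity analysis, and limit conclusions to these pharmacists.

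Trial status says recruitment is over and results are being analysed, so the sample size can no longer be changed. The article should acknowledge that it contains no allowance for pharmacist variation.

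Costs:

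- **Precision.** Intervals widen, slightly if the ICC is near zero and substantially with few pharmacists and a larger ICC (about 8% to nearly threefold in the cases worked above).
- **Blinding.** Only intervention patients have a pharmacist, so pharmacist identity reveals allocation to a statistician who is meant to be blinded. The model must be fixed in writing before that variable is released. The pharmacist model already planned needs the same variable, so the problem exists either way.

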**Fig. 2 Fig2:**
[figure not shown]
Schedule of enrollment, interventions and assessments

### Outcomes

#### Primary outcome measurements

##### Treatment adherence

There are two modes of assessing treatment adherence, i.e., medication adherence and rehabilitation/physical therapy adherence. Both modes will be assessed after 3 months (week 12) from baseline (week 0). The Urdu version of the General Medication Adherence Scale (GMAS) [1] will be used for the assessment of adherence to medication and pharmacotherapy. The scale consists of eleven items that measure a patient’s adherence to medication and provide a score that could be interpreted as high, good, partial, low or poor adherence. There are four possible choices for each item, i.e., always, mostly, sometimes or never, which give a score of 0, 1, 2 or 3, respectively [22]. Adherence to rehabilitation/physical therapy will be assessed by utilizing the Urdu version of the General Rehabilitation Adherence Scale (GRAS). The scale consists of eight items that measure a patient’s adherence to physical therapy and provide a score that could be interpreted as high, good, partial, low or poor adherence. There are four possible choices for each item, i.e., always, mostly, sometimes or never, which give a score of 0, 1, 2 or 3, respectively ([name]: Development and validation of General Rehabilitation Adherence Scale (GRAS) in patients undergoing physical therapy for various musculoskeletal diseases. (unpublished work).

##### Knowledge of rheumatoid arthritis

Patient knowledge of RA will be assessed after 3 months (week 12) from baseline (week 0). The Rheumatoid Knowledge Assessment Scale (RAKAS) will be used to measure knowledge of RA disease. The RAKAS is a 13-item scale that contains questions related to knowledge, symptoms, treatment and risk factors. The items are multiple-choice questions (MCQs) and a correct answer awards a score while the wrong answers provide no score. A cumulative score is calculated, which is interpreted as excellent, good, low or poor knowledge ([name]: Development and validation of a novel Rheumatoid Arthritis Knowledge Assessment Scale (RAKAS) in Pakistani patients with rheumatoid arthritis. (unpublished work).

#### Secondary outcomes

##### Health-related quality of life (HRQoL)

The Urdu version of the 5-level European Quality of Life Scale (EQ-5D-5 L) will be used for assessing HRQoL. The EQ-5D-5 L is a generic tool to measure health and provides a numeric value for the patient’s health status. The scale comprises two parts, i.e., the descriptive health profile and the EQ visual analogue scale (VAS). The first component measures quality of life in the domains of mobility, self-care, usual activities, pain/discomfort and anxiety/depression. It measures patients’ responses on 5 different levels, i.e., having no problem, mild problem, moderate problem, severe problem and being unable/have extreme problem. The second component, EQ VAS, measures health status on a scale with two extreme points, i.e., best imaginable health and worst imaginable health. Patients are required to indicate their self-perceived health status on the scale. The score is then calculated as per the criteria specified by EuroQol [23, 24].

##### Direct cost of treatment

The mean direct cost of RA treatment after 3 months (week 12) from baseline (week 0) will be calculated in patients enrolled in the CG and in the IG. We consider direct cost of treatment as the cost incurred for appointments with rheumatologists, follow ups, medications and rehabilitation/physical therapy, aimed at minimizing any disease-related impairment [25, 26]. This will be documented using a specially designed data collection form.

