**Methods/design:**

This is a randomized, single-blind, two-arm, controlled trial in patients with rheumatoid arthritis visiting outpatient rheumatology clinics in Karachi, Pakistan. We will enroll patients with established diagnosis of rheumatoid arthritis over 3 months. The patients would be randomized through a computer-generated list into the control group, i.e., usual care or into the intervention group, i.e., pharmaceutical care, in a ratio of 1:1, after providing signed written consent. The study will take place in two patient-visits over the course of 3 months. Patients in the intervention group would receive intervention from the pharmacist while those in the control group will receive usual care. Primary outcomes include change in mean score from baseline (week 0) and at follow up (week 12) in disease knowledge, adherence to medications and rehabilitation/physical therapy. The secondary outcomes include change in the mean direct cost of treatment, HRQoL and patient satisfaction with pharmacist counselling.

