### Study plan

The process will start after patients attend the study explanation session and consent to participate. The patients who refuse to participate will be provided regular hospital care. Patients who consent to participate will sign the patient consent form and will be screened for eligibility. Ineligible patients will be excluded from the study and given regular hospital care. Eligible patients will be randomized by computer software into the IG or CG. Patients’ baseline data will be recorded. Enrolled patients’ demographic data will be documented at baseline. Patients will have their anthropometric measurements, i.e., weight, height, etc. noted in addition to their socio-demographic data. Moreover, the patients will be assessed for the outcome measures. The patients randomized into the IG will be provided pharmacist intervention. At the follow-up appointment, i.e., after 3 months (week 12) from baseline (week 0), the same data will be recorded from patients in both treatment groups.

Attention is paid to achieving high patient-retention rates by comprehensively briefing the patients and answering their queries. In the case of loss to follow up, the rheumatologist and the hospital’s front desk staff will establish contact with the patient, try to convince them to participate and if not, document the reason for leaving the study. The whole study will encompass two visits in due course (Fig. 1).

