Outcome selection is an important area in designing clinical trials. The selected outcome must be relevant to patients, health care professionals and policy makers. Appropriate outcomes help in evaluating, disseminating and generalizing the findings of a trial [34]. There is a plethora of studies that evaluate disease knowledge, medication adherence and quality of life as prime treatment outcomes for chronic illnesses [4, 11, 32, 33]. However, treatment in RA may include rehabilitation/physical therapy to minimize mobility-related problems as a consequence of disease. It is worthwhile mentioning that rehabilitation/physical therapy was reported as an outcome by Kirkham and colleagues in their observational review of randomized trials over the last 50 years [34]. Therefore, adherence to rehabilitation/physical therapy is considered as another treatment outcome in our study. Thus, the primary outcomes are change in mean scores for disease knowledge, medication adherence and rehabilitation/physical therapy adherence. Since RA mostly affects middle-aged individuals, studies report that this age group is mostly affected with respect to productivity, which may add to the financial burden on the patient. Therefore, a change in the mean direct cost of treatment and patients’ HRQoL were considered as secondary outcomes.

One of the most important elements to assess in studies that evaluate the impact of counselling on treatment outcomes is the quality of counselling. Patient satisfaction could be considered as an indirect indicator of quality of service. Not only is it important from a subjective point of view, but this satisfaction could translate into future visits, trust and recommendation to others, thereby increasing the likelihood of pharmaceutical care delivery among the masses. Saleem and colleagues mentioned the absence of this indicator as a limitation in their study [11]. Therefore, patient satisfaction with pharmacist counselling is designated as another secondary outcome.

As of now, there have been no trials conducted in Pakistan that evaluate the effectiveness of a multi-dimensional pharmacist intervention in improving treatment outcomes in patients with RA. The results of this trial could set the foundation for future delivery of care for such patients in Pakistan and in other parts of the globe.

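### Direct cost is worded as a level in one place and a change in others, and its confirmatory test is a within-arm before-after test that needs equal costing periods and never compares the arms

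*Protocol article*

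**What the plan says.** All references are to the protocol article.

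- **Outcomes, Direct cost of treatment:** "The mean direct cost of RA treatment after 3 months (week 12) from baseline (week 0) will be calculated" in each arm. The components are the "cost incurred for appointments with rheumatologists, follow ups, medications and rehabilitation/physical therapy". On recording: "This will be documented using a specially designed data collection form". That form is not among the documents.
- **Abstract, Methods/design:** "The secondary outcomes include change in the mean direct cost of treatment".
- **Discussion:** the secondary outcome is "a change in the mean direct cost of treatment".
- **Statistical analysis:** the confirmatory analysis is a Wilcoxon signed-rank test, applied alike to knowledge, adherence and "the cost of treatment after 3 months, i.e., baseline within-subject analysis". The Mann-Whitney comparison of the two groups at the same time point is labelled descriptive.
- **Study plan:** at baseline, "Moreover, the patients will be assessed for the outcome measures", and the same data are recorded at week 12 in both arms.
- **Inclusion criteria:** RA must have been diagnosed at least 3 months before invitation.

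**The concern.** Two things look wrong.

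First, a mean level per arm and a within-patient change are different endpoints with different variances. The text supports either.

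Second, cost is put through the same paired test as the questionnaire scores. A knowledge or adherence score exists at a visit, whereas cost exists only over a period. A paired difference in cost has a meaning only when both figures cover the same length of time, and the article gives neither length. If the baseline figure covers a shorter period, the test picks up the difference in period length and reports it as a rise in cost in both arms.

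At stake is the trial's conclusion on cost. The analysis named as confirmatory could report a change that reflects only how the form asked the question. Even when it does not, it gives no estimate of what the pharmacist's intervention did to cost.

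**Working it through.** **Step 1: the wordings side by side.** The Outcomes section has a level by arm, the Abstract and Discussion a change, and the Statistical analysis section a within-subject difference from baseline. The article prints no figure for cost (no mean, SD or expected effect), so there is none to reproduce.

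**Step 2: what the baseline cost can be.** The Study plan has outcome measures assessed at baseline, so a baseline cost is planned. The section on randomization and allocation concealment has the data collector see patients before the consultation or the intervention. Any non-zero week-0 cost must therefore look back over some earlier period. Its length is not stated.

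**Step 3: how the paired test depends on the two periods.** Inputs:

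- From the article: 619 patients, 20% drop-out, 1:1 allocation, two-sided 5% level. Completers per arm: 619 × 0.8 / 2 = 247.6, taken as 247.
- Assumed: lognormal weekly cost, log-SD 0.8, within-patient correlation 0.5 on the log scale, no change in spending, week-12 figure covering 12 weeks, baseline figure covering w weeks.

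Rejection rate of the signed-rank test within one arm (500 simulated arms per setting):

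| Baseline period w | Rejection |
|---|---|
| 1, 4 or 8 weeks | 100% |
| 11 weeks | 32% |
| 12 weeks | 5.4% |

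A hand check on the log scale agrees in pattern. The expected log difference is ln(12/w). Its standard error is 0.8 × √(2 × (1 − 0.5)) / √247 = 0.8 / 15.7 = 0.051.

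- w = 8: 0.405 / 0.051 = 7.9, so rejection is practically certain.
- w = 11: 0.087 / 0.051 = 1.7, so rejection is possible but not certain.
- w = 12: 0, so rejection is at the nominal 5%.

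With a 4-week baseline period, the apparent rise is 12/4 − 1 = 200%.

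**Step 4: a second cost model.** Assumed: lognormal monthly cost, between- and within-patient log-SD 0.5 each, a 3-month figure at week 12, 300 trials per setting. Arms had 247 patients, or 309 (619 / 2 without drop-out).

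| Baseline period | Within-arm signed-rank | Between-arm Mann-Whitney on week-12 cost |
|---|---|---|
| 3 months | 4.0% to 5.5% | 5.3% to 5.7% |
| 2.5 months, 1 month, 0.33 month or zero cost | 100% | 3.3% to 7.7% |

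The between-arm test of week-12 cost does not use the baseline figure, so a mismatch in periods cannot affect it. Its scatter around 5% is simulation error.

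**Step 5: level or change when the periods are equal.** Let rho be the correlation between baseline and week-12 cost, with equal variances. Relative to the variance of the week-12 level, a change score has variance 2(1 − rho), and a baseline-adjusted comparison has 1 − rho².

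| rho | Change score | Baseline-adjusted |
|---|---|---|
| 0.3 | 1.40 | 0.91 |
| 0.5 | 1.00 | 0.75 |
| 0.7 | 0.60 | 0.51 |

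The choice of endpoint therefore affects precision even without a period mismatch. Adjustment is the most precise of the three at each of these values.

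**Step 6: what the test compares.** A signed-rank test within an arm compares patients with themselves. Significance in one arm, in both or in neither does not estimate the difference between arms, whatever the periods.

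**The case against.** The timing wording in the Outcomes section is the article's stock phrase. It is used also for adherence, knowledge and satisfaction, where it marks when an outcome is measured. A reader might infer that cost is defined as the amount spent between week 0 and week 12, so that no cost can exist at week 0 and the paired test must give a false change. The documents do not support that. The phrase need not mean accrual, the Study plan provides for a baseline record of the same data, and the diagnosis criterion makes a matching three-month look-back possible for every patient. The level and change wordings can also be reconciled as week-12 cost set against baseline cost.

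The costing period may well be on the data collection form or in the full protocol. Its absence from a journal article is not in itself a fault. A mismatch in periods would also affect both arms alike, and a between-group test is planned.

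All of that stands. What it does not remove is the choice of method that the article does state. The confirmatory test for an accruing quantity is a within-arm before-after test, and the comparison that would survive a mismatch is only descriptive. No detail on the form would turn the within-arm test into a comparison of the arms.

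**Conclusion.** The point holds as a fault in the stated analysis of one secondary outcome. The article words cost as a level and as a change, and it rests the confirmatory analysis on a test that is valid for cost only with equal costing periods and does not compare the arms even then.

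The false change is conditional. With unchanged spending, rejection is about 5% per arm with equal periods, 32% with 11 weeks against 12 under the first cost model, and about 100% with clearly unequal periods under both. These rates rest on assumed lognormal costs, because the article gives no cost data. The failure to compare the arms rests on no such assumption. It would be wrong to say that the trial has no baseline cost, or that its cost result will be spurious.

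The change is worth making. The Trial status section says that results are already being analysed, so the definition should be settled without sight of the cost results by arm.

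**What to change.** Use one definition in the Abstract, the Outcomes section, the Statistical analysis section and the Discussion: direct cost per patient over the 12 weeks to the week-12 visit.

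Make the confirmatory analysis for cost the between-arm difference in mean cost with a 95% CI. State the period that the baseline cost covers. If it is an equal 12-week period, enter baseline cost as a covariate. If it is any other length, do not subtract it from the week-12 figure. Do not use the within-arm before-after test as confirmatory for cost.

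The cost is wording in four places and one regression model, with no new patients or visits. The downside is that the result can no longer be presented as a before-after saving.
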